### Data analysis

3.9.

An intention-to-treat analysis will be performed. A descriptive analysis of the variables will be carried out, with frequency and percentage for the qualitative variables; mean and standard deviation for the quantitative normal distributed variables and median and quartiles for the quantitative not-normal distributed variables. The values from the scores for the intervention and the control group will be compared with the *t*-student test if the score is normally distributed, with the Mann–Whitney test if the score is not-normally distributed and if the score has a cut-off, it will be compared with chi-square test. The effect size will be calculated as the difference of means and with ratio of proportions (with its corresponding confidence intervals).

A linear regression and a logistic regression will be considered including other variables that can affect the response. Also, we will stratify the results for other factors like gender, age and others than will be considered. To check normality, the Kolmogorov–Smirnov test and the Shapiro–Wilk test will be used. All the confidence intervals will be performed with a 95% confidence level. All the analysis will be performed with the software R version 4.2.2.

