### Sample size calculation

3.6.

Standard deviation (SD) of the primary outcome CYRM-32 scale was used to estimate the minimum sample required to detect a 10-point difference in the scale between the intervention and control groups.

Taking into account an SD of 20 of the CYRM-32 scale, accepting an alpha risk of 5%, power of 80% and a follow-up loss rate of 10%, it would be necessary a minimum of 70 students/group. GRANMO tool (Antaviana, 2011) was used to calculate the sample size.

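### The tests fixed in section 3.9 under an intention-to-treat label use, as written, only students with a score at that visit and ignore T1; a T1-based, cluster-aware model should be the main analysis

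*Protocol article*

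**What the plan says.** Section 3.9 (Data analysis) opens with "An intention-to-treat analysis will be performed" and does not define the set further. It then fixes the comparison: "The values from the scores for the intervention and the control group will be compared with the" t-test if the score is normally distributed, with Mann-Whitney if it is not, and with chi-square if the score has a cut-off. The effect size is a difference of means or a ratio of proportions. On adjustment it says only this: "A linear regression and a logistic regression will be considered including other variables that can affect the response". T1 is not named among those variables.

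Section 3.6 (Sample size calculation) allows for loss: "power of 80% and a follow-up loss rate of 10%, it would be necessary a minimum of 70 students/group".

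Section 3.3 sets three assessments (T1 at baseline, T2 after the six weeks, T3 24 weeks later) and has teachers see that questionnaires are completed. Section 4 (Discussion) reports 674 participants from eight randomised schools, four of which received the intervention.

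**The concern.** A two-sample test needs an observed score from each student it compares. A student with T1 but no T2 or T3 contributes nothing to it, and for students who are followed the T1 score is set aside. The plan expects about one student in ten to be lost, so a reader of section 3.9 alone would run the tests on those observed and report the result as intention-to-treat.

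That matters if the reasons for loss differ by arm. Section 3.8 says participants and research team are not blinded. Under section 3.4 only one arm has weekly nurse-led sessions. If low-resilience pupils were lost more often in one arm, that arm's observed mean would be too high, and the tests as stated have no means of correcting it. The T1 scores that could correct it are already collected.

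**Working it through.** **1. The plan's own figure.** Inputs from section 3.6: difference 10, SD 20, alpha 5% (taken as two-sided), power 80%, loss 10%.

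n = 2 × (1.96 + 0.8416)² × 20² / 10² = 62.8, so 63 per group. 63 / 0.9 = 70. The stated figure reproduces. The 80% power therefore rests on 63 students per group with an observed score.

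**2. Expected loss in the recruited sample.** 10% of 674 is about 67 students without a follow-up score. With an equal split (assumed), 337 × 0.9 ≈ 303 per arm are observed.

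**3. Bias of the unadjusted observed-score difference.** Assumptions: baseline and follow-up scores are bivariate normal with SD 20. Their correlation r is 0.695, the two-month stability figure in section 3.5.1.1, with 0.5 as a lower assumed value because T3 is much later. Loss is 10% per arm, unrelated to score in one arm and related to low baseline in the other.

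Bias = SD × r × (mean standardised baseline among those retained in the affected arm).

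| Loss in the affected arm | Mean standardised baseline of retained | Bias, r = 0.695 | Bias, r = 0.5 |
|---|---|---|---|
| Odds ratio 1.5 per SD lower baseline | 0.040 | 0.56 | 0.40 |
| Odds ratio 2 | 0.066 | 0.92 | 0.66 |
| Odds ratio 3 | 0.098 | 1.36 | 0.98 |
| Exactly the lowest tenth lost (extreme) | 0.195 | 2.71 | 1.95 |
| Unrelated to score | 0 | 0 | 0 |

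The first three cases at r = 0.695 are about 6% to 14% of the 10-point target.

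**4. Does using T1 remove it?** I simulated the four biased cases at r = 0.695 with one million students per arm. A linear regression of the follow-up score on arm and T1, fitted to the observed students alone, had bias within 0.03 points of zero in every case. Here loss depends only on T1, so adjusting for T1 is enough.

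**5. Size against the standard error.** Ignoring clustering, SE = 20 × √(2/303) = 1.62. With about 303/4 ≈ 76 observed per school and assumed intracluster correlations of 0.02 and 0.05, the design effect 1 + (76 − 1) × ICC is 2.5 and 4.75, so the SE is about 2.6 and 3.5. The three odds-ratio cases are then about 0.2 to 0.5 SE and the extreme case about 0.8 to 1.1 SE. The unclustered SE would give 0.3 to 0.8, and 1.7 in the extreme case, which overstates the ratio.

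**6. Loss that T1 does not explain.** If the 10% lost from the intervention arm would have scored d points below that arm's observed students, with no such gap in the control arm, an observed difference of 10 becomes 10 − 0.1 × d in all students: 9.5, 9 and 8 for d = 5, 10 and 20. Equal gaps in both arms cancel.

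**The case against.** A reader might infer something stronger: that the plan contradicts itself, and that its intention-to-treat result simply is a completers' result, with the 10% allowance as proof. The document does not support that. No section excludes anyone or defines a completers' set. Inflating the sample for expected loss is standard, protects power, and is compatible with intention-to-treat. The label may mean only that students are analysed as allocated, and a t-test does that for a pupil who skips sessions but fills in the questionnaire. A t-test can also follow imputation, which section 3.9 neither plans nor rules out.

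The missing-data method may stand in the analysis plan, which is not shown although the Discussion mentions one, so its absence from the article is no fault. Nothing in the document shows that loss differs by arm. Section 3.3 has teachers ensuring completion, and section 3.4.2 gives both arms the same questionnaires in the same period. Section 3.9 does contemplate regression, and a T1-adjusted regression is enough when loss depends only on T1.

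All of this stands. What it does not meet is the narrower point. The article goes beyond silence: it commits to unadjusted tests on the scores and leaves the adjusted analysis optional, without naming T1. That is a choice of method, and a better one is available from data already planned.

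**Conclusion.** The point holds as a weak choice of main analysis, not as a contradiction or a sample size error. The committed tests, taken as written, use observed scores only and discard T1, in a trial that expects 10% loss.

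The cost is conditional. It is about 0.6 to 1.4 CYRM-32 points at r = 0.695, 0.4 to 1.0 at r = 0.5, and 2 to 2.7 in the extreme case. It is zero if loss is unrelated to score. Once clustering is counted, the ordinary cases are a fraction of a standard error. These figures rest on assumed loss that differs by arm, a correlation measured over two months, and assumed intracluster correlations. The change is worth making because it is cheap, not because a large bias has been shown.

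**What to change.** In section 3.9:

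- State that all enrolled students are analysed in the arm to which their school was allocated.
- Make the main analysis a model that uses T1. One option is a likelihood-based mixed model of the T1, T2 and T3 scores, in which students with only T1, or T1 and T2, still contribute. The other is a regression of the follow-up score on arm and T1, which is simpler but leaves out students without that follow-up score.
- In either case include a random effect for school (and classroom), or an equivalent cluster adjustment with a small-sample correction, since only eight schools were randomised. A model without this would still ignore the design.
- Report the two-sample test under the name of an unadjusted observed-score analysis.
- Add one sensitivity analysis that shifts the missing scores in one arm, for example from 0 to −10 points. At 10% loss this moves the difference by up to 1 point.

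The cost is wording and a little more work in R, with no new data and no change to the 70 per group on this point. The main analysis would rely on missing-at-random, which the shift analysis probes. The Discussion says T1 and T2 data are already being analysed, so the change should be dated and reported as made at that stage.

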### Design

3.1.

This study is a cluster-randomized controlled trial with parallel arms. Clusters will be school classrooms (grades 6, 7), subjects aged 12-to-15 years.

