### Randomization

3.7.

Eligible schools will be randomly assigned to the intervention or control group. The clusters will be school classrooms (grades 6 and 7). For each grade (6 and 7) there will be several classrooms (clusters) depending on the schools. The randomization procedure will be performed in two steps. First, the schools will be randomly allocated either to an intervention group or control group by the external researcher using computer-generated random numbers; second, the external researcher will randomize the intervention group into the different school levels.

According to the minimum estimated sample size (70 participants/group) and knowing that there are 25 to 30 students per classroom, we will need a minimum of three clusters (classrooms) per group.

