In the application of this intervention, we consider some limitations. On one hand, the effect of the intervention may be lost in the long term. However, a 24 weeks follow-up is proposed to assess the maintenance of the effect and see if it is necessary to include reinforcement or repeat the intervention after 1 or 2 years to maintain resilient results. On the other hand, there may be some disparities in the effectiveness of the intervention between schools due to the different teams involved. If this is the case, we will propose to improve the trainings so that the teams act as similarly as possible.

Once the intervention will be applied, we will be able to assess its effectiveness. We expect to increase resilience in adolescents at risk and prevent mental health problems through this school-based intervention. Once the effectiveness is demonstrated, nurses from different fields such as primary health care or mental health specialists will have access to the program to be implemented in schools or other sites that work with adolescents at risk. This intervention will give new tools to nursing professionals to increase resilience and coping skills for facing adverse situations during adolescence.

Currently, we have finished the recruiting period and the trial status is “active” at www.clinicaltrials.gov. At the end of the recruitment, we had a total sample of 674 participants from eight randomized schools. The intervention was carried out in 4 schools from January 2022 to spring 2022. We are analyzing the initial data from control and intervention groups at T1 (baseline) and T2.

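### Schools are randomised, but the planned tests treat students as independent, so p-values and confidence intervals will be far too optimistic

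*Protocol article*

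**What the plan says.** Section 3.1 (Design) states: "This study is a cluster-randomized controlled trial with parallel arms". Section 3.7 (Randomization) sets the unit of allocation: "First, the schools will be randomly allocated either to an intervention group or control group". The Discussion reports the outcome of recruitment, "we had a total sample of 674 participants from eight randomized schools", and adds: "The intervention was carried out in 4 schools from January 2022 to spring 2022". That leaves four control schools.

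Section 3.9 (Data analysis) fixes the comparison of arms. It begins "The values from the scores for the intervention and the control group will be compared with the" and continues with Student's t-test for normally distributed scores, the Mann-Whitney test for the others, and the chi-square test where a score has a cut-off. Effects are to be given as mean differences and ratios of proportions with 95% confidence intervals. Linear and logistic regression with further covariates are to be considered, as is stratification by gender, age and other factors.

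The article nowhere mentions an ICC, a design effect, random effects, GEE, cluster-robust standard errors or a cluster-level analysis. Sections 3.1 and 3.7 call classrooms the clusters, although section 3.7 allocates schools.

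**The concern.** The t-test, the Mann-Whitney test and the chi-square test, applied to student scores, assume independent observations. Students in one school share teachers, neighbourhood and nurse team, so their scores are likely to be correlated. The article itself points that way. Its Discussion anticipates that effectiveness may differ between schools because different teams deliver the programme, and section 3.4.2 lets control activities vary by school.

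The arm contrast therefore carries between-school variance, estimated from eight schools with 8 − 2 = 6 degrees of freedom. The stated t-test behaves as if there were 674 − 2 = 672. Neither the 5% error rate nor the 95% coverage is then delivered. The result matters in practice: offering the programme to the waitlisted control schools, and releasing it more widely, both depend on the trial showing that it works.

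**Working it through.** **The plan's own sample size first.** Section 3.6 gives a difference of 10 points on the CYRM-32, SD 20, alpha 5%, power 80% and 10% loss. For two individually randomised groups with two-sided alpha, n = 2 × (1.96 + 0.84)² × 20² / 10² ≈ 63 per group, and 63/0.9 = 70. This reproduces the stated 70 per group exactly, with no design effect. One-sided alpha would give 50, or 56 after loss, which does not match. Clustering is thus absent from the sample size as well as from the analysis.

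**Inputs for the check.** There are 674 students in 8 schools (Discussion), so m = 674/8 = 84.25 per school and 337 per arm, taking equal school sizes. SD 20 comes from section 3.6. The ICC is not given in the article; 0.005 to 0.10 is my assumption.

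**Formulas.**
- Design effect: DE = 1 + (m − 1) × ICC. At ICC 0.02, 1 + 83.25 × 0.02 = 2.67.
- The student-level standard error is too small by a factor of √DE.
- True two-sided error of a nominal 5% test: 2 × (1 − Φ(1.96/√DE)).
- Student-level standard error: 20 × √(2/337) = 1.54, so the student-level 95% half-width is 1.96 × 1.54 = 3.02 points.
- Cluster-adjusted half-width: 2.447 × 1.54 × √DE, where 2.447 is the 97.5% point of t on 6 degrees of freedom.

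| Assumed school ICC | DE | √DE | True type I error | Adjusted 95% half-width (points; student-level 3.02) |
|---|---|---|---|---|
| 0.005 | 1.42 | 1.19 | 10.0% | 4.49 |
| 0.01 | 1.83 | 1.35 | 14.8% | 5.10 |
| 0.02 | 2.67 | 1.63 | 23.0% | 6.15 |
| 0.05 | 5.16 | 2.27 | 38.8% | 8.57 |
| 0.10 | 9.33 | 3.05 | 52.1% | 11.51 |

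**Simulation.** With 4 schools per arm, 84 students per school, no true effect and 4,000 runs per ICC, the rejection rates were:

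| School ICC | t-test | Mann-Whitney | t-test on school means (6 df) |
|---|---|---|---|
| 0 | 4.8% | 5.0% | 4.6% |
| 0.01 | 15.1% | 15.0% | 5.3% |
| 0.02 | 22.6% | 22.0% | 5.3% |
| 0.05 | 37.5% | 36.5% | 4.6% |
| 0.10 | 52.5% | 50.9% | 5.5% |

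The simulation agrees with the formula, and the Mann-Whitney test gives no protection. Adding classroom variance to school variance (assuming 3 classes of 28 per school) raised the t-test's error further, from 16.7% (school 0.01, classroom 0.01) to 43.1% (school 0.05, classroom 0.03).

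**Sensitivity.**
- With 10% loss, m falls to about 75.8 and the error is 13.8%, 21.5% and 36.8% at ICC 0.01, 0.02 and 0.05.
- If correlation acted only within classrooms of 27.5 students (midpoint of the 25 to 30 in section 3.7), the error would be 6.6%, 8.1%, 11.3%, 19.9% and 30.5% across the five ICC values.

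**The case against.** The strongest reply has four parts.

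1. The regressions are only to be considered, and a school or classroom term is neither named nor excluded. An analysis plan that is not shown could supply one. This stands for the regressions, where independence is inferred. It does not help the t-test, Mann-Whitney and chi-square tests. Section 3.9 names them for the comparison of arms, so a separate plan would have to overrule that text rather than complete it.
2. The unit of clustering is not settled. Section 3.7 adds a second randomisation step, by school level within the intervention group, and the article calls classrooms the clusters. Allocation by school is the better reading, given eight randomised schools of which four delivered the programme, but the wording needs to be reconciled. Even classroom-only clustering leaves the error above 5%.
3. The size of the problem rests on an assumed ICC. That is true. The direction does not depend on its value as long as it is positive, and at 0.005 the error rate has already doubled.
4. The binary case is hypothetical, since no cut-off is defined for any outcome. This stands and limits the chi-square part of the point. The primary resilience scores are unaffected.

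Recruiting far more than 140 students is no defence. More students per school improves precision but also raises the design effect, so it makes the student-level test less valid.

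**Conclusion.** The concern holds. The stated tests do not fit the stated design, and this is a wrongly fixed method rather than a detail left to another document. With eight schools of about 84 students, a nominal 5% test has a true type I error of about 15% to 39% for a school ICC of 0.01 to 0.05, and standard errors are understated by factors of 1.35 to 2.27. A properly adjusted 95% interval at SD 20 is about 1.7 to 2.8 times as wide as the planned one (5.10/3.02 to 8.57/3.02). These figures assume equal school sizes, school as the level of allocation and the stated ICC range. As written, the primary p-value and interval would not support a claim of effectiveness, so this must be corrected before results are reported.

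**What to change.** Rewrite section 3.9 and any separate analysis plan as follows.

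- **Continuous outcomes:** a linear mixed model with a fixed effect for arm, random intercepts for school and for classroom nested in school, and Kenward-Roger or Satterthwaite degrees of freedom.
- **Check:** a t-test on the eight school means with 6 degrees of freedom, which held its error rate at about 5% in simulation.
- **Binary outcomes, if any cut-off is used:** a cluster-adjusted model with a small-sample correction. Four schools per arm are too few for uncorrected GEE or robust standard errors.
- **Reporting:** take every confidence interval from these analyses and report the estimated ICC.
- **Cluster unit:** reconcile sections 3.1 and 3.7 with the school-level allocation, and explain the second randomisation step. Adjusting for classroom alone would not be enough.

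The work is a rewording and a few lines of R, with no new data. The statistical cost is wider intervals and lower power. With 337 per arm, SD 20 and 6 degrees of freedom, power for a 10-point difference is about 98%, 91% and 67% at an ICC of 0.01, 0.02 and 0.05. The Discussion says baseline and first post-intervention data are already being analysed, so the change should be dated and reported as made after access to data.

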#### Primary outcomes

3.5.1.

The level of resilience is the primary outcome, assessed using principally the Child youth resilience measure-32 (CYRM-32; Llistosella et al., 2019). Additionally, the Brief resilience scale (BRCS; Limonero et al., 2014) will be used.

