##### Depressive symptoms

3.5.2.2.

Depressive mood will be asked as follow: *“Are you depressed or sad?.”* It was adapted from the “Are you depressed?” Screening for depression in the terminally ill (Chochinov et al., 1997). It evaluates through a numerical scale of 0–10 (0-not depressed, 10-worst possible depression).

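### The test for each scale score is chosen by a normality pre-test, and the Mann–Whitney branch gives a p-value that does not belong to the stated difference of means

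*Protocol article*

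**What the plan says.** All the rules on testing are in section 3.9 of the protocol article.

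- **Choice of test.** Scores judged normal are compared by a Student t-test, and the others by the Mann–Whitney "test if the score is not-normally distributed and if the score has a cut-off, it will be compared with chi-square test". The last clause is a third route.
- **Gate.** "To check normality, the Kolmogorov–Smirnov test and the Shapiro–Wilk test will be used". The article does not say which test governs, or whether normality is judged within arm or on the pooled sample.
- **Effect measure.** "The effect size will be calculated as the difference of means and with ratio of proportions", each with a confidence interval. No effect measure is attached to the Mann–Whitney test. Non-normal variables are described by median and quartiles.
- **Regression.** Linear and logistic models with other variables are mentioned only as something to be considered.

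Two other sections set the target. Section 3.5.1: "The level of resilience is the primary outcome, assessed using principally the Child youth resilience measure-32". Section 3.6 gives the sample needed "to detect a 10-point difference in the scale between the intervention and control groups". Section 3.5.2.2 adds a single mood item: "It evaluates through a numerical scale of 0–10". The Discussion reports 674 participants from eight randomised schools, four of which received the intervention, with T1 and T2 data already being analysed.

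**The concern.** The trial was sized on, and will report, a difference of means. The test that produces the p-value is nevertheless left to the observed distribution. If a score is judged non-normal, readers would see medians in the descriptive table, a rank-based p-value, and a difference of means with its interval. The p-value and the interval address different quantities and can fall on opposite sides of 5%.

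The gate also depends on sample size. A normality test that usually passes mild skew at 70 students will usually fail it at several hundred, although the comparison of means becomes more robust as numbers grow. With two gate tests and no order between them, the same data can lead to either comparison, and the same scale can be tested differently at T2 and T3. Personnel are not blinded (section 3.8) and analysis has begun, so the choice of primary test should not remain open.

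**Working it through.** **1. The plan's own sample size.** Inputs from section 3.6: difference 10, SD 20, alpha 5% (two-sided assumed), power 80%, loss 10%.

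n = 2(z₀.₉₇₅ + z₀.₈₀)² × SD² / difference² = 2 × 7.849 × 400/100 = 62.8, so 63 per group; 63/0.90 = 70. The stated 70 reproduces as a comparison of two means.

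**2. Each branch against the stated effect measures.**

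| Branch | What the test addresses | Listed effect measure |
|---|---|---|
| t-test | equality of means | difference of means: matches |
| Mann–Whitney | whether values in one arm tend to exceed those in the other | none |
| Chi-square | equality of proportions | ratio of proportions: matches, but it is not the 10-point difference that sized the trial |

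**3. How often the gate would switch.** The documents give an SD of 20 for CYRM-32 and no distribution for any scale, so these shapes are assumptions:

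- CYRM-32 type: 32–160, mean 115 or 125, SD 20, negative skew.
- BRCS type: 4–20, mean 13, SD 3, negative skew.
- Mood item: 0–10, mean 3.5, SD 2.8, positive skew.

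Skew was 0, 0.3 or 0.5 in size before rounding and truncation at the scale limits. There were 500 simulated samples per setting, tested at the 5% level. Entries are rejection rates across the settings.

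| Score | Test | n = 70 | n = 337 | n = 674 |
|---|---|---|---|---|
| CYRM-32 type | Shapiro–Wilk | 6–43% | 14–100% | 67–100% |
| CYRM-32 type | Kolmogorov–Smirnov | 0–1% | 0–16% | 0–64% |
| BRCS type | Shapiro–Wilk | 17–47% | 100% | 100% |
| BRCS type | Kolmogorov–Smirnov | 3–9% | 89–100% | 100% |
| 0–10 item | Shapiro–Wilk | 98–100% | 100% | 100% |
| 0–10 item | Kolmogorov–Smirnov | 5–17% | 100% | 100% |

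The 337 is 674/2 and assumes equal arms. Kolmogorov–Smirnov was run with standard p-values after standardising by the sample mean and SD, which is conservative. A version corrected for that estimation would reject more often. The article does not say which version is meant.

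**4. Whether the gate is needed, and what Mann–Whitney costs.** At 63 per arm with skew 0.5, the t-test's type I error was 4.8%. For a 10-point shift, with skew 0, 0.5 and 1.0, power was 78.8%, 78.7% and 79.1% for the t-test and 77.1%, 79.5% and 83.6% for Mann–Whitney. The gate protects little, and the rank test loses little.

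**5. The chi-square branch, only if a cut-off is used.** Take a normal score, SD 20, shifted by 10, with the cut-off midway between the group means: p₁ = 1 − Φ(0.25) = 0.401 and p₂ = 0.599.

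n = [1.960√(2 × 0.5 × 0.5) + 0.842√(0.401 × 0.599 + 0.599 × 0.401)]² / 0.1974² = 3.878/0.03897 = 99.5, so 100 per group; 100/0.90 gives 112.

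- Cut-off 1 SD above the control mean: 124 (138 with loss).
- Cut-off 1.5 SD above: 185 (206 with loss).
- Power at 63 per group: 60%, 51% and 37% for the three positions, against 80% for means.
- At 337 per group taken as independent, chi-square power is still 97–99.9%.
- With an assumed ICC of 0.05: design effect 1 + (674/8 − 1) × 0.05 = 5.16 and 337/5.16 = 65.3 effective per group. Power is then 81.5% for means and 61.9% for chi-square at the best cut-off.
- Over an assumed ICC of 0.01–0.10: 99.8–57% for means and 97–39% for chi-square at the best cut-off.

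**The case against.** The strongest reply is that section 3.9 does not make the difference of means depend on the normality result. A mean-based estimate with its interval may therefore be reported in every case. Under the pure location shift implied by section 3.6, the t-test and Mann–Whitney respond to the same shift. This limits the harm but does not remove the mismatch. A bounded score with a ceiling need not shift uniformly, and the p-value would still come from a different comparison than the interval.

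Four stronger readings are tempting, and the documents do not support them.

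- *That the plan will certainly switch at this sample size.* No score distribution or arm sizes are given, and Kolmogorov–Smirnov often would not reject for a CYRM-32-type score.
- *That chi-square replaces the analysis of the primary outcome and discards its information.* No cut-off is stated for any scale, the sentence can be read as adding a categorical comparison, and chi-square does match the listed ratio of proportions.
- *That Mann–Whitney wastes power.* It does not, to any material degree.
- *That the gate is what keeps baseline and school out of the test.* The t-test cannot carry them either, and regression is mentioned, though weakly.

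Which normality test prevails is a detail that an analysis plan could settle, and the Discussion says one was developed. The gate itself is stated in the article and is not an omission.

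**Conclusion.** The concern holds in limited form. The article lets a normality check choose the test for each scale score, while the effect it states for scores and the difference that sized the trial are both on the mean scale. The Mann–Whitney branch is left without a matching estimate.

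Under the assumed shapes at 674 participants, that branch is likely for CYRM-32 if Shapiro–Wilk governs (67–100%), much less so if Kolmogorov–Smirnov governs (0–64%), and nearly certain for the four-item scale and the 0–10 item. If normality is judged within arms of about 337, the Shapiro–Wilk range for CYRM-32 widens to 14–100%.

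The cost is a mismatched p-value and a data-dependent choice, not lost power. The loss from chi-square (63 to at least 100 per group) is conditional on a cut-off that the article never gives, so it is not shown to affect the primary outcome. This should be changed, but it does not by itself invalidate the trial.

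**What to change.** Delete the normality gate from section 3.9. For each scale score, at T2 and at T3, name one analysis in advance and keep it whatever the normality result. It should be a difference of means with 95% CI from a baseline-adjusted model that accounts for the randomised school, with a small-sample correction for eight schools, and the p-value should come from that same model. Inspect residuals as a diagnostic only.

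As a sensitivity analysis, add a permutation test over school allocations. With four of eight schools there are 8!/(4! × 4!) = 70 splits, so the smallest two-sided p-value is 2/70 = 0.029. The reference set must follow the allocation actually used, including the second step in section 3.7.

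Keep any cut-off comparison as supportive, with the cut-off and its scale named beforehand.

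The cost is a rewritten analysis section and one sensitivity analysis, with no new data. Because T1 and T2 data are already being analysed, the revision must be dated and disclosed as made after access to data.
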